## Abstract

**Introduction:**

Irritable bowel syndrome (IBS), known as a functional and organic gastrointestinal disorder, is a collection of symptoms that occur together and generally include pain or discomfort in the abdomen and changes in bowel movement patterns. Due to the limitations of conventional treatments, alternative IBS treatments are used by many patients worldwide. Samryungbaekchulsan (SRS), a herbal formula, has long been used for alleviating diarrhoea-predominant IBS (D-IBS) in traditional Korean medicine. Otilonium bromide (OB) is an antimuscarinic compound used to relieve spasmodic pain in the gut, especially in IBS. Although herbal formulae and Western drugs are commonly coadministered for various diseases in Korea, few clinical studies have been conducted regarding the synergic effects of these treatments for any disease, including D-IBS.

**Methods and analysis:**

This trial is a randomised, double-blinded, placebo-controlled, double-dummy, four-arm, parallel study. After a 2-week preparation period, 80 patients with D-IBS will be randomly assigned to one of four treatment groups consisting of SRS (water extract granules, 5 g/pack, three times a day) with OB (tablet form, one capsule three times a day) or their placebos, with treatment lasting for 8 weeks. Post-treatment follow-up will be conducted 4 weeks after the end of treatment. The primary outcome is the finding obtained using the Subject’s Global Assessment of Relief method. The secondary outcomes are the severity of symptoms related to D-IBS, determined using a 10-point scale, and the change in symptoms.

**Ethics and dissemination:**

This trial has full ethical approval of the Ethics Committee of Catholic Kwandong University International St. Mary’s Hospital (IS15MISV0033) and the Korean Ministry of Food and Drug Safety (30769). The results of the study will be disseminated through a peer-reviewed journal and/or conference presentations.

**Trial protocol version:**

IS15MISV0033 version 4.0 (25 July 2016).

**Trial registration number:**

KCT0001621 (approval date: 10 August 2015).

Strengths and limitations of this studyThis randomised controlled trial is the first Korean clinical trial approved by the Korean Ministry of Food and Drug Safety to investigate the efficacy and safety of Samryungbaekchulsan (SRS; herbal formula) and otilonium bromide (OB; Western drug) in diarrhoea-predominant irritable bowel syndrome (D-IBS).To evaluate the therapeutic effect and safety of the coadministration of SRS and OB, this study is proposed as a double-blind, double-dummy, four-arm, parallel-group randomised controlled trial.The primary outcome is the improvement in the patient’s symptoms according to the Subject’s Global Assessment of Relief, and the secondary outcome is the severity of D-IBS symptoms.This study is conducted with a small sample size (four arms, 20 participants per group), so further clinical trials with powerful sample sizes will be required to more adequately determine the effectiveness of SRS and/or OB in D-IBS.

## Introduction

Irritable bowel syndrome (IBS), a chronic gastrointestinal (GI) disease and functional bowel disorder, is characterised by abnormal bowel habits and abdominal pain without structural, morphological and histological abnormalities. It affects approximately 20% of the population worldwide, according to population-based studies.^1–6^ In addition, recent evidence suggests that IBS is not only a functional disease but also an organic disease with a complex of symptoms, including infection, immune activation, serotonin dysregulation, bacterial overgrowth, central dysregulation, brain–gut interaction and genetics.^4–8^ Based on their predominant bowel habits, patients with IBS can be divided into diarrhoea-predominant IBS (D-IBS), constipation-predominant IBS or mixed IBS.^2 6 9^ Recently, smooth muscle relaxants, bulking agents and antidiarrhoeal agents have been used in the treatment of IBS.^10^ However, these methods are often not effective, and many patients with IBS also use complementary treatments, such as herbal medicine, acupuncture, psychological treatment and lifestyle correction.^2 11 12^

Samryungbaekchulsan (SRS; Shenlingbaizhu-san in traditional Chinese medicine; Jinryobyakujutsu-san in Kampo medicine), which was introduced in the famous classical compendium of herbal formulae ‘Formulary of Peaceful Benevolent Dispensary’, consists of 10 herbs (Atractylodes rhizoma Alba, Poria sclerotium, Dioscoreae rhizoma, Glycyrrhizae radix et rhizoma, Coicis semen, Nelumbinis semen, Platycodonis radix, Dolichoris semen, Amomi fructus and Ginseng radix). In traditional Korean and Chinese medicine, this herbal formula has been used to treat GI disease, and various studies have been published regarding the treatment of IBS with SRS.^13–18^ SRS has been shown to have antiacetylcholine and antibarium chloride effects and to suppress gastric secretion and small intestine motility.^13^ However, no clinical trials have evaluated the efficacy of SRS for IBS when coadministered with a conventional drug.

Otilonium bromide (OB) is widely used for the prevention and reduction of symptoms in patients with IBS.^7 8^ OB has been shown to inhibit L-type and T-type calcium channels, muscarinic receptors and tachykininergic responses in human cultured smooth muscle cells and rat colon strips.^19–21^ According to a recent randomised controlled trial (RCT), OB (40 and 80 mg) is more effective for treating IBS than placebo, not only for the reduction of bloating and abdominal pain but also for protection from relapse owing to its long-lasting effect.^22 23^

According to the guidelines of the Korean Society of Gastroenterology, antispasmodic agents are recommended for the treatment of D-IBS (grade 1B),^24^ and SRS is the preferred drug for diarrhoea treatment in Korean medicine.^18^ Recently, several studies have been conducted to evaluate the therapeutic effect of the coadministration of herbal formulae and conventional drugs for IBS in China.^25 26^ However, there has been no such clinical study in Korea, even though both herbal medicine and conventional drugs are widely used for IBS treatment in the clinical field. Therefore, there is a need to evaluate the efficacy and safety of SRS, OB and the coadministration of both drugs.

In this study, we expect that the combined administration of OB and SRS will result in synergistic effects that improve D-IBS symptoms, including abdominal pain, discomfort (the main effect of OB) and diarrhoea-like stool patterns (the main effect of SRS).

## Methods and analysis

### Objectives

The purpose of this study is to evaluate the efficacy and safety of the coadministration of SRS and OB to patients with D-IBS.

### Necessity of the trial

Recently, herbal medicines and Western drugs have been coadministered for various medical therapies. This is particularly true in Korea, where approximately 76% of patients have used the combination of herbal medicines and Western drugs.^14^ However, only a few studies have evaluated the interaction between Western and herbal medicines. Despite the need for combined treatment in patients with various diseases, there are no standard clinical guidelines or scientific evidence regarding coadministration because of a lack of research and data.

D-IBS is a disease that is difficult to cure, and many patients require treatment with both Western and herbal drugs to experience an improvement in their symptoms. Therefore, it is very important to conduct a clinical study regarding the efficacy and safety of the combined administration of SRS and OB in patients with D-IBS.

### Basis of drug selection

According to guidelines for IBS treatment, the OB recommendation level is high (ie, the level of evidence is moderate and many experts recommend using it), and it is the most reasonable treatment option.^25^ SRS is the herbal formula used most often by clinical Korean and Chinese medical doctors for abdominal pain, abdominal discomfort and chronic diarrhoea, which are typical symptoms of D-IBS.^15–17 24^ Based on these studies and clinical applications, OB and SRS were selected for this trial.

### Hypothesis

We hypothesise: (1) that coadministration of SRS and OB will have a more positive effect on D-IBS symptoms than either SRS or OB alone; (2) that after 8 weeks of treatment with SRS, OB or both drugs, the Subject’s Global Assessment of Relief and severity of D-IBS symptoms will be more improved than after treatment with placebo and (3) that coadministration of SRS and OB will be safe for patients with D-IBS.

### Design

This study is a placebo-controlled, double-blind trial. Eighty patients will be enrolled and randomly assigned to four separate arms of the trial. The trial will be conducted at Catholic Kwandong University International St. Mary’s Hospital, Incheon, South Korea.

The study subjects will be required to participate in a 2-week preparation period (weeks −2 to 0) and an 8-week drug-administration period (weeks 0–8). The patients will visit four times, on weeks 0, 4, 8 and 12. The primary outcome measurement will be evaluated at weeks 2, 4, 6, 8 and 12, and the secondary outcome measurement will be evaluated at weeks 0, 2, 4, 6, 8 and 12. Participants will be assessed for efficacy and safety of the treatment through visits (0, 4, 8 and 12 weeks) and telephone questionnaires (2 and 6 weeks). In addition, laboratory tests will be conducted at 0, 4 and 8 weeks. According to the intervention protocols, the clinical research coordinator (CRC) will encourage patients and participants to complete follow-up at every visit.

During the drug-administration period, SRS or its placebo will be given as one pack of water extract granules three times a day, 30 min before each meal. OB or its placebo will be given as one tablet three times a day, 30 min before each meal.

Participants will be divided into four groups: (1) SRS and OB group, (2) SRS and placebo-OB group, (3) placebo-SRS and OB group and (4) placebo-SRS and placebo-OB group. The entire flow chart of the study is shown in figure 1.

**Figure 1 F1:**
[figure not shown]
Flow chart of trial. D-IBS, diarrhoea-irritable bowel syndrome; FM, family medicine; GIIM, gastrointestinal internal medicine; OB, otilonium bromide; P, placebo; SRS, Samryungbaekchulsan.

This study received the first approval given by the Korean Ministry of Food and Drug Safety (KMFDS) for a study of the coadministration of a conventional drug and a Korean traditional herbal medicine (approval number: 30769).

Potential participants will be provided with sufficient information about the study, and only those who agree to the study protocol and sign the consent form will be enrolled. The study will be implemented according to Good Clinical Practice and the revised version of the Declaration of Helsinki.

### Sample size calculation

This trial is a study for a new therapeutic regimen of SRS and OB combination treatment. In a similar study conducted previously by using coadministration of a probiotics mixture and an herbal medicine (placebo-controlled, double-blind and randomly four-arm trial), each arm consisted of at least 15 patients, and the total sample size was more than 60 participants.^27^ In other similar studies, clinical trials have been conducted with a total of 60–64 participants, consisting of 12–30 patients per group.^28–30^ Based on these previous studies, the minimal clinical significance of the trial can be obtained when only 16 participants complete the trial. Because the dropout rate is expected to be 20%, each trial group will be made up of at least 20 participants. Therefore, the total sample size must be more than 80 participants.

### Inclusion criteria

The following patients would be included: (1) patients aged 18–75 years; (2) patients satisfying the Rome III criteria of IBS (recurrent abdominal pain or discomfort that began at least 6 months before the clinical trial, with a rating of more than 3 on a 10-point scale, frequency of at least 3 days/month in the last 3 months and associated with two or more of the following: improvement associated with defecation, onset associated with a change in frequency of stools and onset associated with a change in form of stool)^1 9^; (3) patients satisfying the Rome III criteria of IBS, whereby D-IBS type is defined as loose/mushy or watery stools—Bristol Stool Form (BSF) Scale 6–7 ≥2 times/week^1 30^; (4) patients with a negative urine pregnancy test (in women of a childbearing age, within 7 days before the clinical trial) and who consent to using contraception during the administration period; (5) patients with the ability to read the symptom questionnaire and understand it and (6) patients who agree with the clinical plan and voluntarily sign the institutional review board (IRB)-approved documents.

### Exclusion criteria

The exclusion criteria are as follows: (1) chronic liver disease (cirrhosis, chronic hepatitis B or C); (2) chronic renal failure or renal impairment (serum creatinine ≥2 times the upper limit of normal); (3) liver dysfunction (aspartate aminotransferase (AST)/alanine aminotransferase (ALT) ratio ≥3 times the upper limit of normal); (4) diabetes (haemoglobin A1c >8% or not controlled by diet or medication), hypertension (≥160/100 mm Hg), thyroid dysfunction (exceptions in the following cases: if the disease is controlled by drug administration with a stable dose for 12 weeks before the screening, and the drug dose remains constant during the trial period), clinically significant haematological, cardiac, pulmonary or neurological disorders, or other severe systemic disorders; (5) abnormal findings on colonoscopy or colonography within the last 5 years; (6) history of surgery that affects GI motility (ie, gastrectomy, colonic resection, hysterectomy, except for appendectomy); (7) GI disease characterised by the following symptoms within 6 months before the clinical trial: inflammation of or ulcer in the oesophagus, stomach or duodenum; gastro-oesophageal reflux disease (at the discretion of the examiner, subjects may enrol if the disease is chronic and not acute); GI bleeding; GI stenosis or closure; infectious diarrhoea; inflammatory bowel disease (ie, Crohn’s disease, diverticulitis, ulcerative colitis, infectious enteritis, ischaemic colitis); pancreatic insufficiency; biliary abscess; (8) mental illness or an addiction to drugs or alcohol; (9) severe systemic organ diseases such as cancer, autoimmune disease, stroke (although patients in remission for more than 5 years from a cancer unrelated to the GI tract can participate in the trial); (10) pregnancy, breast feeding and unwillingness to use contraception during the trial; (11) a history of taking the following drugs within 2 weeks before the trial: antibiotics, analgesics, antidepressants, antianxiety agents, anti-inflammatory agents, antiulcer agents, antigastric secretion inhibitors, laxatives, antispasmodics, antacid agents, GI stimulants, prostaglandin agents and corticosteroids; (12) use of medications that do not match the intent of this trial or have a clinical interaction with SRS or OB; (13) lactose intolerance (not controlled by food); (14) glaucoma; (15) participation in other clinical studies within 30 days prior to clinical screening and have received other clinical trial medications (including placebo); (16) hypersensitivity to clinical trial medicines and (17) other reasons considered inappropriate for participation in clinical trials.

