#### Statistical analysis

The statistical analysis will be conducted by blinded professional statisticians. To evaluate the efficacy of the study, both an intent-to-treat (ITT) analysis (primary analytical method) and a per-protocol (PP) analysis (secondary analytical method) will be performed. The ITT analysis will be conducted for all patients who were followed up at least once after randomisation and will be able to be evaluated for effectiveness. The PP analysis will be performed for patients who complete the 8-week treatment course and meet the inclusion and exclusion criteria.

To analyse the continuous variables in the demographic information and pretreatment characteristics between groups, a one-way analysis of variance (ANOVA) and Kruskal-Wallis test will be conducted. An ANOVA and Kruskal-Wallis test will also be used to test for symptom improvement compared with baseline (0 week) and the variables for analysis that include the following: (1) subjective symptom improvement (primary outcomes) and (2) severity of symptoms related to D-IBS (abdominal pain, abdominal discomfort, satisfaction of defecation, frequency of abdominal pain and quality of life). All values will be shown as mean±SEM. Comparisons of outcome assessments between the four groups will be performed using the paired t-test or Wilcoxon signed-rank test.

If the Subject’s Global Assessment of Relief on the Likert scale is ‘0’ or ‘1’ for more than 2 weeks between weeks 8 and 12, then the symptoms will be considered to have improved sufficiently. Based on this, we will calculate the symptom relief rate by dividing the number of participants who exhibited sufficient symptom relief by the total number of participants in the trial and present descriptive statistics. The CATMOD procedure will be used to evaluate the improvement of symptoms compared with baseline. Comparisons between the four groups will be conducted using the χ^2^ test or Fisher’s exact test. These statistical analyses will also be performed at 2, 4, 6, 8 and 10 weeks from baseline. The Cochran-Mantel-Haenszel test will be used to confirm the difference between the intervention groups at each time point.

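### The liver exclusion sets an AST/ALT quotient against an upper limit of normal, so read literally it lets through proportionate rises in both enzymes

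*Protocol article*

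**What the plan says.** In the protocol article, under Exclusion criteria, item (3) excludes "liver dysfunction (aspartate aminotransferase (AST)/alanine aminotransferase (ALT) ratio ≥3 times the upper limit of normal". The item directly before it, on the kidney, reads "chronic renal failure or renal impairment (serum creatinine ≥2 times the upper limit of normal": one measured analyte against its own limit.

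The other exclusion specific to the liver is item (1), "chronic liver disease (cirrhosis, chronic hepatitis B or C", which rests on diagnosis. Item (17) is a discretionary clause, "other reasons considered inappropriate for participation in clinical trials". Neither names an enzyme value. No other section gives an entry limit for AST or ALT, and none gives an upper limit for their quotient.

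Two other sections depend on the criteria or bear on the safety aim. Under Hypothesis, the third hypothesis is that the combination is safe. Under Statistical analysis, the per-protocol set consists of patients who "complete the 8-week treatment course and meet the inclusion and exclusion criteria". According to Trial status, recruitment is still open.

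**The concern.** A limit stated as a multiple of the upper limit of normal belongs to a measured concentration. Here it is attached to the quotient of two concentrations. The slash alone could mean either enzyme, but the word that follows the enzyme names makes the tested quantity a quotient. A quotient reflects the balance between the enzymes and says nothing about how high they are, so the rule can let through the patients it sets out to exclude.

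This is a rule stated in full that gives the wrong answer when followed, which is different from a detail left to a longer document. At stake are entry to a trial whose aims include the safety of a drug and herb combination, and membership of the per-protocol set. If staff apply what they take to be the intended meaning, neither is fixed by the written criterion.

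**Working it through.** The article states no figure that could be reproduced here, so the check is of the criterion's arithmetic.

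**Inputs from the article.** The tested quantity is AST/ALT. The multiple is 3, from Exclusion criteria (3).

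**Assumptions, because the article gives no values.** Let u be the upper limit for AST divided by the upper limit for ALT, taken as 0.8 to 1.25. Let R be an upper limit for the quotient itself, taken as 1.0 to 2.0. R = 1.0 is the same as testing whether the bare quotient is at least 3.

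**Formula.** Write AST as a times its own limit and ALT as b times its own limit. Then

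quotient = (a/b) × u, and the patient is excluded if (a/b) × u ≥ 3R.

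If a = b, the quotient equals u however large a is. The size of a shared rise therefore drops out.

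**Results.**

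| AST (× its limit) | ALT (× its limit) | Quotient, u = 0.8 to 1.25 | R = 1.0 (needs 3) | R = 1.5 (needs 4.5) | R = 2.0 (needs 6) |
|---|---|---|---|---|---|
| 3 | 3 | 0.8 to 1.25 | not excluded | not excluded | not excluded |
| 5 | 5 | 0.8 to 1.25 | not excluded | not excluded | not excluded |
| 10 | 10 | 0.8 to 1.25 | not excluded | not excluded | not excluded |
| 10 | 5 | 1.6 to 2.5 | not excluded | not excluded | not excluded |
| 5 | 10 | 0.4 to 0.63 | not excluded | not excluded | not excluded |
| 20 | 4 | 4.0 to 6.25 | excluded | excluded for u = 1.0 and 1.25 | excluded for u = 1.25 only |
| 0.9 | 0.2 | 3.6 to 5.6 | excluded | excluded for u = 1.0 and 1.25 | not excluded |

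**How AST-dominant a rise must be.** Rearranged, exclusion needs a/b ≥ 3R/u. The smallest value over the assumed ranges is 3 × 1.0/1.25 = 2.4, and the largest is 3 × 2.0/0.8 = 7.5. Below 2.4, no patient is excluded under any of these assumptions, whatever the height of the enzymes.

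**The reverse error in units.** With R = 1.0 and an assumed limit of 40 U/L for each enzyme, AST 36 and ALT 11 are both normal, yet 36/11 = 3.27 is above 3 and the patient is excluded.

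**Contrast, not a proposed rule.** If the same multiple were read against each enzyme separately, the first six rows would meet it and the last would not. The two readings disagree in all of the first five rows, and in the last two rows for some assumed limits. The choice of reading therefore decides eligibility.

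**The case against.** The strongest reply is that this is a slip in a condensed article. The governing text is protocol version 4.0, which is not shown, and the trial plan was reviewed by the ethics board and the Korean regulator. A reader who drops one word gets a familiar criterion, and nothing suggests that anyone chose to screen on a quotient. I accept that this is the likeliest explanation. It lowers the weight of the point but does not remove it, because the published rule is complete as written and gives the wrong result if followed.

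Four stronger readings are tempting, and the article does not support them.

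- **That the rule excludes nobody with both enzymes raised.** A strongly AST-dominant rise, such as 20 and 4 times the limits, can meet it under some assumed limits.
- **That liver injury present at entry would be counted as an on-treatment abnormality.** Under Design, "laboratory tests will be conducted at 0, 4 and 8 weeks", so a week 0 value exists for comparison. The Laboratory tests section acknowledges differing individual baselines, plans no detailed laboratory statistics and leaves causation to the investigator's judgement of each patient.
- **That sites would apply the rule differently.** The Design section names one hospital. Staff there could still read the line in two ways.
- **That patients with liver injury have been enrolled.** The article does not show how the criterion has been applied. Items (1), (4), (8), (9) and (17) also give an investigator grounds to exclude a patient who is plainly ill. None of them sets an enzyme limit, so they do not repair item (3).

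It is also fair to say that the per-protocol analysis is secondary to intent-to-treat, and that the number of patients affected cannot be estimated from the article.

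**Conclusion.** The point holds in limited form. As written, criterion (3) tests a quantity for which the article gives no upper limit. Read literally, it does not exclude proportionate, ALT-dominant or moderately AST-dominant rises. Both enzymes at 3 to 10 times their limits give a quotient of about 1. With the limit of the quotient taken as 1, it could exclude a patient whose enzymes are both normal.

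That a shared rise cancels needs no assumption. The ranges rest on the assumed u of 0.8 to 1.25 and R of 1.0 to 2.0.

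The consequence is confined to eligibility, and through it to safety at entry and per-protocol membership. For scale, the Sample size calculation section counts on 16 completers per group, so one reclassified completer is 1/16 = 6.25% of a group. A reader might infer that the main efficacy result is compromised, but nothing in the article shows an effect on power, sample size or the primary intent-to-treat analysis. The line should be corrected while recruitment is open.

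**What to change.** Reconcile criterion (3) with the full protocol. Have the investigators confirm which quantity is compared with which limit, and reword the line so that the measured quantity and its upper limit of normal match, as they do in criterion (2), "renal impairment (serum creatinine ≥2 times the upper limit of normal". The cut-off itself is for the investigators to confirm and is not proposed here.

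If the operative protocol carries the same wording, obtain ethics board approval for the change, as the Protocol amendments section requires. Before the per-protocol set is fixed, check patients already enrolled against the confirmed wording.

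The cost is one line of text, a possible amendment during recruitment, and a review of entry laboratory values. These should already be on file, assuming that both enzymes were measured in order to apply criterion (3).

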### Intervention

The herbal formula SRS is commonly used by Korean traditional medical doctors for the treatment of diarrhoea and related diseases.^13–18^ SRS used in this study (Samryungbaekchulsan granule; Han Kook Shin Yak, Nonsan, South Korea) is extracted with water and mixed with starch and lactose in accordance with Korean Good Manufacturing Practice. Production of SRS is regulated and allowed by the KMFDS. SRS contains 10 herbs, listed in table 1. Placebo-SRS is made from cornstarch and has the same taste, shape, colour and similar scent as SRS. SRS and placebo-SRS will be sealed in identical aluminium bags with the same labelling. These herbal drug packages will be distributed by an independent pharmacist in an isolated room. According to the recommended dosing methods of KMFDS, after SRS or placebo-SRS is dissolved in boiled water, the subjects will take them 30 min before each meal (5 g/pack, three times a day).

**Table 1 T1:** Ingredients in the herbal formula Samryungbaekchulsan

Scientific name	Part used	Grams per day
Atractylodes rhizoma Alba	Root	3.0
Poria sclerotium	Dried core	4.0
Dioscoreae rhizoma	Root	3.0
Glycyrrhizae radix et rhizoma	Root	1.5
Coicis semen	Seed	8.0
Nelumbinis semen	Fruit	4.0
Platycodonis radix	Root	2.5
Dolichoris semen	Seed	4.0
Amomi fructus	Fruit	2.0
Ginseng radix	Root	3.0

OB (Menoctyl Tab; Dong Hwa Pharm, Seoul, Korea) is a tablet containing OB 40 mg. Placebo-OB is a tablet made of Ludipress with the same taste, shape and colour as OB. Patients will be instructed to swallow one tablet of OB or placebo-OB 30 min before each meal over the administration period. The drugs used in the trial (SRS, OB, placebo-SRS, placebo-OB) have been approved by the KMFDS. Patients will be asked at the end of the study whether the drugs that they have been taking are either real or placebo, to measure the success of blinding. Compliance will be confirmed by counting returned SRS packets or OB tablets. Every patient will be instructed to write down any adverse events during the administration period, and these records will be evaluated at the follow-up. At the patient visits (at 0, 4 and 8 weeks), we will perform a check of vital signs, physical examination, ECG and laboratory tests to evaluate safety for the patients. All side effects will be reported to the investigator.

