#### Secondary outcomes

At 2, 4, 6, 8 and 12 weeks from the start of the treatment period, patients will be assessed for severity of D-IBS symptoms (abdominal pain, abdominal discomfort, satisfaction of defecation, frequency of abdominal pain, quality of life) using a Likert scale ranging from 0 to 10.^31^ Patients will also be instructed to record the number of defecations per day, BSF and the degree of force used in bowel movements at 0, 2, 4, 6, 8 and 12 weeks.^32^

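### Exclusion 13 admits patients whose lactose intolerance is controlled by diet, although SRS granules contain lactose and placebo-SRS is described only as cornstarch; the criterion and the product are poorly matched

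*Protocol article*

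**What the plan says.** All statements are in the protocol article.

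- **Exclusion criteria, item 13:** "13) lactose intolerance (not controlled by food". The words in brackets narrow the exclusion, so intolerance that diet does control is not a bar to entry.
- **Intervention, active granule:** SRS "is extracted with water and mixed with starch and lactose in accordance with Korean Good Manufacturing Practice". The amount of lactose is not given.
- **Intervention, placebo granule:** "Placebo-SRS is made from cornstarch and has the same taste, shape, colour and similar scent as SRS". Lactose is not mentioned.
- **Intervention, dosing of both granules:** "the subjects will take them 30 min before each meal (5 g/pack, three times a day".
- **Design:** "an 8-week drug-administration period (weeks 0–8", with four groups: "1) SRS and OB group, (2) SRS and placebo-OB group, (3) placebo-SRS and OB group and (4) placebo-SRS and placebo-OB group".
- **Outcomes:** a global relief score at weeks 2, 4, 6, 8 and 12; 0 to 10 ratings that include abdominal pain and discomfort; and diary items under which patients "record the number of defecations per day, BSF and the degree of force used in bowel movements".

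**The concern.** A patient qualifies under item 13 because diet keeps lactose out. The study granule then supplies lactose by a route that diet does not control. Lactose intolerance can cause loose stools, abdominal pain and discomfort, which are the symptoms this trial measures.

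Two things are at stake. First, some patients may have avoidable bowel symptoms. Second, if only the active granule carries lactose, those symptoms arise in groups 1 and 2 and not in groups 3 and 4. The relief question asks for change since before the trial, so a patient who entered well controlled for lactose and then reacted would score worse for a reason unrelated to the herbs. The effect would run against SRS and the combination, and would add gastrointestinal adverse events in those groups.

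**Working it through.** **1. The plan's own group size.** 16 completers / (1 − 0.20) = 20 per arm, and 4 × 20 = 80. This reproduces and is not in dispute. Two arms receive active SRS: 2 × 20 = 40 patients.

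**2. Which comparisons are affected, taking the placebo description at face value.**

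| Comparison | Lactose from granules | Differential? |
|---|---|---|
| Combination vs OB alone (1 vs 3) | first only | yes |
| SRS alone vs double placebo (2 vs 4) | first only | yes |
| Combination vs double placebo (1 vs 4) | first only | yes |
| Combination vs SRS alone (1 vs 2) | both | no |
| OB alone vs double placebo (3 vs 4) | neither | no |

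This touches one of the two contrasts in hypothesis 1 and two of the three in hypothesis 2.

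**3. Lactose dose.**
- Granule mass: 3 × 5 g = 15 g/day. Lactose is therefore above 0 and below 15 g/day. The article supports nothing tighter.
- Illustration: Table 1 sums to 35 g/day of herb. That exceeds the granule mass, so it is taken here as weight before extraction.
- Assumed extract yield of 10% to 30% (not in the document): extract is 3.5 to 10.5 g/day, leaving 15 − 3.5 = 11.5 down to 15 − 10.5 = 4.5 g/day for starch plus lactose.
- Assumed lactose share of that remainder, 10% to 75%: from 0.10 × 4.5 = 0.45 g/day to 0.75 × 11.5 = 8.6 g/day.
- The article gives no amount of lactose that provokes symptoms, so this range cannot be turned into a symptom rate.

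**4. Number of patients.**
- Assumed prevalence p of diet-controlled intolerance among those enrolled: 5% to 30%. Assumed share r who react: 25% to 100%.
- Affected patients = 40 × p × r, from 40 × 0.05 × 0.25 = 0.5 to 40 × 0.30 × 1 = 12 of the 40 on SRS.
- Chance that at least one such patient is among the 40, even at p = 5%: 1 − 0.95^40 = 0.87.
- One affected patient is 1/20 = 5% of an arm, or 1/16 = 6.25% of the planned completers.
- The mean on-treatment score in an SRS arm moves by p × r times the change in an affected patient, that is by 0.0125 to 0.30 of that change.

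These ranges show a direction and a strong dependence on unstated inputs. They are not an estimate.

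**5. Timing.** Dosing stops at week 8. The Statistical analysis section defines sufficient relief by scores between weeks 8 and 12, almost wholly off drug. Any excipient effect should therefore be looked for in the week 2 to 8 scores, ratings and stool records, which the same section also analyses by time point.

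**The case against.** **The two statements do not contradict each other.** This is right. A partial exclusion and a list of excipients can both be true, and the authors evidently considered lactose intolerance and drew a line. What remains is that the line is tied to diet while the study granule adds lactose outside it.

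**The difference between arms is read from silence.** A one-line placebo description in a condensed article need not be a full excipient list, and plain cornstarch would hardly match a ten-herb granule in taste, colour and scent. The excipients of the OB tablet and the composition of the placebo-OB base are not given either, so total lactose by arm cannot be judged. This stands as a condition on the between-arm effect. It does not remove the eligibility problem: if placebo-SRS does contain lactose, the difference shrinks but the exposure extends to all four arms.

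**Other exclusions cover it.** Item 16 concerns hypersensitivity to the trial medicines, and item 17 leaves the matter to judgement. Neither overrides the specific wording of item 13.

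**An excipient effect is part of the marketed product's effect, and it would not create false efficacy.** This is fair. It is a reason to avoid the word bias without qualification, and the direction is indeed against SRS.

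**A stronger reading to resist.** A reader might infer a measurable loss in the relief rate. For example, if 5% to 20% of patients are affected and all lose a response they would have had at a 50% rate, the loss is 0.5 × 0.05 to 0.5 × 0.20, or 2.5 to 10 percentage points. The document supports none of these inputs, and the defined relief rate is measured after dosing ends.

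**Conclusion.** The point holds as a mismatch between an eligibility criterion and the stated composition of the study granule. It is not a contradiction and not a demonstrated bias. From the text alone, patients with diet-controlled lactose intolerance may enrol, and those allocated to SRS receive lactose three times a day for 8 weeks.

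The further step, that resulting symptoms would weigh against SRS on on-treatment relief, symptom and stool outcomes and on gastrointestinal adverse events, depends on two conditions: placebo-SRS is lactose-free as described, and the lactose per pack is enough to cause symptoms. The document settles neither. The size is therefore unknown and may be small. With 20 per arm, even one or two affected patients would be 5% to 10% of an arm, which is why a cheap correction is worthwhile. It is a modest improvement rather than a threat to the trial's validity.

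**What to change.** Reconcile exclusion 13 with the Intervention section in one of two ways:

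1. Remove the bracketed exception in item 13 for patients still to be enrolled. Trial status says recruitment is ongoing, and Protocol amendments describes the approval route.
2. Alternatively, confirm and state that the lactose content of SRS and placebo-SRS is matched or negligible. Matching alone removes the difference between arms but not the exposure.

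For patients already randomised, where lactose intolerance was recorded at screening, add a sensitivity analysis of the primary comparison that omits those patients from all four arms. Because the characteristic precedes randomisation, omitting them everywhere introduces no post-randomisation selection. Report the week 2 to 8 results alongside, since that is when exposure occurs.

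Cost: a one-line amendment or a statement of composition, a slightly smaller recruitment pool under the first option, and one extra analysis. Few patients are likely to inform that analysis, and the article does not say whether lactose history was recorded in usable form.
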